## Abstract

**Introduction:**

Most potential kidney transplant donors in the UK are aged over 60 years, yet increasing donor age is associated with poorer graft survival and function. Urgent preimplantation kidney biopsy can identify chronic injury, and may aid selection of better ‘quality’ kidneys from this group. However, the impact of biopsy on transplant numbers remains unproven. The PreImplantation Trial of Histopathology In renal Allografts (PITHIA) study will assess whether the introduction of a national, 24 hours, digital histopathology service increases the number, and improves outcomes, of kidneys transplanted in the UK from older deceased donors.

**Methods and analysis:**

PITHIA is an open, multicentre, stepped-wedge cluster randomised study, involving all UK adult kidney transplant centres. At 4-monthly intervals, a group of 4–5 randomly selected clusters (transplant centres) will be given access to remote, urgent, digital histopathology (total intervention period, 24 months). The trial has two primary end points: it is powered for an 11% increase in the proportion of primary kidney offers from deceased donors aged over 60 years that are transplanted, and a 6 mL/min increase in the estimated glomerular filtration rate of recipients at 12 months post-transplant. This would equate to an additional 120 kidney transplants performed in the UK annually. Trial outcome data will be collected centrally via the UK Transplant Registry held by NHS Blood and Transplant (NHSBT) and will be analysed using mixed effects models allowing for clustering within centres and adjusting for secular trends. An accompanying economic evaluation will estimate the cost-effectiveness of the service to the National Health Service.

**Ethics and dissemination:**

The study has been given favourable ethical opinion by the Cambridge South Research Ethics Committee and is approved by the Health Research Authority. We will present our findings at key transplant meetings, publish results within 4 years of the trial commencing and support volunteers at renal patient groups to disseminate the trial outcome.

****Trial registration** number:**

ISRCTN11708741; Pre-results.

Strengths and limitations of this studyProspective, randomised evaluation of a clinical service using a novel stepped-wedge cluster design which avoids contamination of trial groups, while remaining acceptable to patients and study centres.The first national, 24 hours streamlined digital histopathology service, which will support all adult kidney transplant centres in the UK and is likely to have applications beyond the trial setting.Example of a low cost ‘registry-based trial’ which uses routinely collected data and has a concomitant economic evaluation to determine cost-effectiveness.Use of two primary end points (and therefore nine possible trial outcomes) increases the possibility of an equivocal, rather than definitive result.To conserve power, the study will not be stopped early except on the grounds of patient safety.Thus, there is a risk that access to histopathology may lead to fewer kidney transplants being performed.

## Introduction

Kidney transplantation is the best treatment for most patients with end-stage renal disease,^1 2^ but shortages in organs mean that patients in the UK wait around 3 years for a transplant.^3^ Over half of the potential pool of deceased donors (people dying in critical care) in the UK are older than 60 years.^4^ Kidneys from donors aged over 60 years have been shown to carry a significantly higher risk of failure than those from younger donors,^5^ and this failure is associated with a substantially increased risk of recipient death.^6^ Consequently, kidneys offered from donors of this age group are less frequently accepted, and once retrieved, are more commonly discarded.^7 8^

### Need for a trial

One approach to assessing which kidneys from older deceased donors (aged >60 years) will provide acceptable long-term function is to perform a biopsy at organ retrieval. The presence of chronic background injury is assessed histologically and its severity can be scored using, for example, the Remuzzi grading system.^9^ Remuzzi has reported that this score correlates with subsequent transplant outcome, and has proposed that, depending on the score the kidney can either be transplanted singly (scores 1–3), discarded (scores≥6) or both kidneys from one donor transplanted into a single recipient (scores 4–5).^9^ One UK transplant centre (Cambridge) has established a preimplantation biopsy service using Remuzzi’s scoring system, but with a modified interpretation of the result. The Cambridge experience demonstrated that kidneys with scores of up to 4 are safe to be used individually, but those with scores of 5–6 should be transplanted together.^10^ Comparison of Cambridge practice to UK transplant activity suggests that this approach resulted in greater numbers of kidney transplants being performed from older donors than would otherwise have been the case.^7^ Outcomes of the transplants were good, in that kidney graft survival from listing was similar to that achieved for all UK deceased kidney transplants—irrespective of donor age.^11^ However, Remuzzi’s approach has not been widely adopted across the UK. One major reservation, which this study will address, is whether biopsy-based selection leads to increased discard rates.^12–14^ In the USA, a large proportion of kidneys are biopsied prior to implantation, and yet discard rates for kidneys from older donors are still high.^15^ In the expectation that preimplantation biopsy analysis is only useful in the subset of deceased donor kidneys in which chronic injury is prevalent, PreImplantation Trial of Histopathology In renal Allografts (PITHIA) will examine transplantation practice for kidneys from deceased UK donors aged over 60 years.

Trial implementation of a national histopathology service is not straightforward. A simple comparison of activity before and after the service is introduced would be unable to distinguish the impact of histopathology from the natural evolution in transplant practice over time. Alternatively, a trial in which individual kidneys are randomised with or without the option to biopsy is not practical. In that study, the availability of extra information for only some kidneys would probably ‘contaminate’ (ie, change) acceptance practice of kidneys offered without it. The pool of elderly deceased kidney donors is already considered high-risk; therefore, implementation of that trial design would be likely to lead to an immediate reduction in acceptance rates for those kidneys offered without a biopsy. The stepped-wedge design addresses these potential problems in two ways. First, the intervention is staggered over the duration of the trial with each centre acting as its own control. Second, at any given centre either all the kidneys will be available to biopsy, or none of them will. This should minimise intracentre contamination effects. Aside from ensuring that the study will have sufficient power to detect differences in the primary outcomes, the stepped-wedge design also has practical advantages over a standard parallel cluster evaluation.^16 17^ The stepped-wedge approach entails that the intervention is rolled out sequentially across the UK, which will allow the trial group time to provide a thorough education programme at each participating centre. This programme will involve a discussion of the indications for, and subsequent interpretation of, the findings of an urgent kidney biopsy. Finally, the design ensures that all centres will eventually gain access to the biopsy service, and patient feedback was strongly in favour of a design which preserved the principle of equity of access.

### Study aims

This paper presents the protocol and rationale for an open, multicentre, stepped-wedge cluster, randomised, registry study. The study will introduce a new, national, histopathology service, and assess the impact of the service on transplant activity and outcomes. A concomitant decision-model based economic evaluation will estimate the lifetime cost-effectiveness of the service.

Specific aims of the study are to:Introduce a national histopathology service for transplantation that uses electronic image transfer to rationalise kidney biopsy processing to a limited number of designated biopsy centres.Perform a randomised evaluation of this service, by staggering its introduction to all the remaining UK renal transplant centres that do not currently have ready access to 24 hours renal histopathology. The evaluation will adhere to the principles of a stepped-wedge cluster randomised study.Determine the cost-effectiveness of this service and thus make recommendations regarding whether it should be continued once the trial is completed, or not.Model a low cost randomised registry study that minimises costs because outcome data are collected centrally, which will shape future transplant research.^18^
This protocol is reported in line with the Standard Protocol Items: Recommendations for Interventional Trials recommendations and has been adapted for publication from the original complete study protocol developed by the Trial Management Group (TMG).^19^

## Methods and analysis

### Description of study design

There will be 22 UK adult kidney transplant centres (each centre representing one cluster) participating in the randomisation. At 4-monthly intervals, a randomly selected group of four or five clusters will be given access to the new histopathology service. Access will enable clinicians to request preimplantation biopsy analysis as a means of evaluating the suitability of kidneys for transplantation. The overall design is presented in figure 1. The study will compare the number of transplants performed, as well as the outcomes of these transplants before and after each centre gains access to urgent histopathology. Every UK adult kidney transplant centre will participate over the 2 years. Cambridge is involved as one of the biopsy processing centres, although outcomes of transplants performed will not be analysed. Cambridge already supports an urgent preimplantation biopsy service, and is therefore beyond clinical equipoise.

**Figure 1 F1:**
[figure not shown]
PreImplantation Trial of Histopathology In renal Allografts schema; stepped-wedge cluster randomised design.

### Study hypotheses

This trial will test the hypothesis: ‘Provision of a national 24/7 preimplantation biopsy service results, at reasonable cost, in transplantation of a greater proportion of kidneys offered from deceased donors aged ≥60 years, and/or improves kidney transplant function at 1-year post-transplant. Numbers of deceased donor kidney transplants performed annually in the UK are consequently significantly increased or improved in quality’.

### Inclusion and exclusion criteria

A biopsy can be requested (at the time of offer) for organs which meet all the inclusion criteria and none of the exclusion criteria. The transplanting surgeon will always decide whether, or not, to biopsy an eligible organ. For the analysis, inclusion criteria are kidneys offered for transplantation from deceased donors (donation after circulatory (DCD) or brain stem (DBD) death) aged ≥60 years. All kidneys offered as a component of a multiorgan transplant are excluded.

### Randomisation

We will use a restricted randomisation technique to randomly allocate the clusters to their cross-over date. To this end, we randomly will select a set of allocation sequences from 10 000 different allocations constrained so that the sum of the total cluster sizes observed under the intervention condition is similar to the total sum of the cluster sizes in the control condition (using historic data). We define ‘similar’ as a difference in the total sums (kidneys) exposed to intervention and control statuses being no different than expected middle 25th percentile range of differences. From this set, one allocation sequence will be selected at random.

Allocation will be performed by an independent statistician once all site approvals are in place and will be revealed to the sites and the trial team approximately 3 months before the date of transition. This approach enables a team of surgeons, renal nephrologists and renal histopathologists to provide a dedicated education package prior to those centres crossing over.

### Intervention and control conditions

#### Control condition

UK renal transplant centres, with the exception of Cambridge, do not undertake urgent, preimplantation biopsy analysis. Therefore, the control condition is standard care, which involves accepting and transplanting kidneys from elderly deceased donors, based on donor clinical history and on macroscopic evaluation of the kidney on retrieval (figure 2). On trial commencement, acceptance and transplant activity of all centres will be monitored prior to their accessing the intervention, as this will establish baseline practice.

**Figure 2 F2:**
[figure not shown]
Logistics for biopsies in the control (2A) and intervention (2B) conditions. eGFR, estimated glomerular filtration rate.

#### Intervention condition

Once a site has transitioned to the intervention condition they will have access to the national histopathology service (figure 2). Implanting surgeons at those transplant centres can then request a kidney biopsy at the time they are offered a kidney via the UK Transplant Registry held by NHS Blood and Transplant (NHSBT) Hub Operations. Requesting a biopsy is not mandatory—the transplant centres can use the service at their discretion. Transplant centres are also not obliged to adhere to a common set of guidelines governing biopsy use; they, along with their patients, retain the final say over whether a kidney should be biopsied, and/or transplanted.

Patients and their representatives have been involved in the design and implementation phases of PITHIA. Ahead of the trial starting, the TMG have met with key national kidney groups who have offered support for the trial by publicising it in their patient-facing publications. Each participating centre has also received a personalised information sheet to provide patients with an overview of the trial and the intended benefits. Final consent for any transplant will be obtained following a discussion of the potential risks and benefits of the individual kidney on offer, in line with standard practice and national guidelines.

### Biopsy method

A punch biopsy tool (5 mm diameter) will be used to take a sample from the upper pole of the kidney. Areas of the kidney which are scarred will be avoided. The 5 mm punch biopsy will be performed at the retrieval operation by the attending National Organ Retrieval Service (NORS) team and placed in formalin. The biopsy will be transported to the most appropriate histopathology centre, which will be determined on a case-by-case basis, with oversight from NHSBT Hub of Operations. Once the biopsy arrives at the processing centre, the on-call biomedical scientist will process the tissue and embed in wax then cut two sections and stain with H&E as well as Periodic Acid Schiff. They will then scan the slide using a 3DHISTECH (Budapest, Hungary) Panoramic DESK scanner at high resolution (0.12 µm/pixel) and upload the files to a secure, centralised server managed by Sysmex UK (Milton Keynes, England).

At the time of protocol submission, there is one other national study using deceased-donor kidney biopsies (QUOD, http://www.quod.org.uk/index.html). A single 5 mm punch biopsy will provide enough material for both purposes and should be halved longitudinally, maintaining full-depth cortical sampling in both pieces.

### Primary outcome measures

Proportion of kidneys aged >60 years that are transplanted on first offer.Estimated glomerular filtration rate (eGFR) measured at 12 months after transplant (acceptable range is between 10 and 15 months after transplant).^20^

### Secondary outcome measures

Proportion of kidneys used overall (all formal offers for donors aged >60 years, not including fast-track offers).Total number of kidney transplants performed.Proportion of kidneys discarded after retrieval, out of all retrieved kidneys.Number and proportion of ‘single’ and ‘dual’ kidney transplants performed.Biopsy utilisation and fidelity, defined as the proportion of kidneys that are biopsied in concordance with the education plan, out of all kidney biopsies.Kidney Donor Profile Index of transplants performed.^21^
Cold ischaemia time, defined as the total time between perfusion of the donor kidneys with cold preservation fluid during retrieval, and reperfusion with recipient blood at implantation.12-month patient survival.12-month graft survival (censored for patient death).Proportion of kidneys diagnosed with primary non-function.Proportion of kidneys diagnosed with delayed graft function (defined as the use of dialysis during the first postoperative week).

#### Safety outcome measures

Biopsy-related complication rate.

*Subgroup analyses* (the primary outcome will be replicated for each subgroup):DBD donors only;DCD donors only;Donors who are aged >70 years;Centres with historically low median UK Kidney Donor Risk Index of transplanted DCD kidneys (low-risk transplants compared with overall UK activity).

The trial will use data that are routinely collected on the national UK Transplant Registry (UKTR), held by NHSBT. The national registry has a mandatory collection system that produces comprehensive information on organ donors, organs, transplants and recipients.

#### Trial closure

The trial will end 12 months after the final clusters have had access to the histopathology service for 4 months (36 months after the start of the trial). This allows 12-month eGFR to be recorded for all kidneys which are eligible for inclusion in the analysis. The trial has no planned early stopping criteria, although the Trial Steering Committee have the power to stop the trial on safety grounds.

### Sample size calculations

Estimates for the sample size calculations were obtained from the UKTR, held by NHSBT. We followed the methodology proposed by Hooper,^22 23^ and this was implemented using SAS (V.9.4, Cary, North Carolina, USA) and the RShiny WebApp (https://clusterrcts.shinyapps.io/rshinyapp/).

#### First primary outcome: proportion of kidneys that are transplanted on first offer

Data were extracted on first kidney offers from potential deceased (DBD and DCD) donors aged 60 years and over, in the UK between 1 April 2014 and 31 March 2016. Offers of simultaneous pancreas kidney, multiorgan, fast-track and any offers to Cambridge were excluded. The percentage of first offers which were transplanted was 28.4%. The median number of first offers per cluster per month was 4.38. A mixed linear regression model was fitted to the extracted data, with a binary outcome (whether the offer resulted in a transplant), a fixed effect for date of offer (which was converted into year quarter, ie, six, 4-month time periods called period henceforth), a random effect for cluster and a random interaction between cluster and period. From this model, the within-period intracluster correlation (WP-ICC) and cluster autocorrelation (CAC) were calculated as 0.03 and 0.92, respectively. Assuming an average cluster-period size of 18, to detect a 11% increase in the number of first offers transplanted, the trial will have 85% power (assuming a significance level of 2.5%) and would represent an increase from 28% to 39% acceptance, which we believe would be considered clinically important. We have not allowed for attrition in this calculation as there is unlikely to be any missing data, due to the robustness of the offering data collected by NHSBT. We checked the sensitivity of this calculation by looking at an increase, and separately a decrease, of 2% in the baseline proportion, by varying the WP-ICC (lower WP-ICC set as 0 and upper WP-ICC set as 0.08) and the CAC (lower CAC set as 0.74 and upper CAC set as 1. The trial has within the region of 80% power for all anticipated values of WP-ICC and CAC, and likely values of cluster-period sizes. The power curve, with the baseline proportion set as 28%, is shown in figure 3A.

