**Figure 3 F3:**
[figure not shown]
(A) Power curve for the first primary outcome, proportion of kidneys that are transplanted on first offer. The curves show the increase in power as the cluster size increases, for 20 clusters, 5 steps, 4 clusters crossing over at each step and the proportion under control and intervention of 28% and 39%, respectively. The black curve shows the power for the base values of within-period intracluster correlation (WP-ICC) and cluster autocorrelation (CAC) (0.03 and 0.92, respectively), and the remaining curves show for lower and upper levels of the WP-ICC (0 and 0.08, respectively) and CAC (0.74 and 1, respectively). (B) Power curve for the second primary outcome estimated glomerular filtration rate measured at 12 months after transplant. The curves show the increase in power as the cluster size increases, for 20 clusters, 5 steps, 4 clusters crossing over at each step and the mean difference of 6 and SD of 16.06. The black curve shows the power for the base values of WP-ICC and CAC (0.06 and 0.08, respectively), and the remaining curves show for lower and upper levels of the WP-ICC (0.01 and 0.11, respectively) and CAC (0.06 and 0.10, respectively).

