#### Second primary outcome: eGFR measured at 12 months after transplant

Data were extracted on all recipients who received a kidney only transplant from deceased donors (DBD and DCD) aged ≥60 years, in the UK (excluding transplants at Cambridge) between 1 April 2014 and 31 March 2016. The median number of transplant recipients per cluster per month was 2, hence providing an average cluster-period size of 8. eGFR was calculated using the 4-variable Modification of Diet in Renal Disease (MDRD) formula using uncalibrated serum creatinine measurements,^20^ hence if missing data were present for the recipients sex, age, ethnicity and serum creatinine at 12 months, then eGFR could not be calculated (19%). The mean eGFR was 41.91 with an SD of 16.06.

A mixed linear regression model was fitted to this data, with a continuous outcome (eGFR), a fixed effect for date of transplant (which was converted into year quarter, ie, six, 4-month time periods), a random effect for cluster and a random interaction between cluster and period. From this model, the WP-ICC and CAC were calculated as 0.06 and 0.08, respectively. Assuming an average cluster-period size of 8 (=2×4 clusters), this outcome will have 89% power to detect a mean difference in eGFR of 6 mL/min (assuming a significance level of 2.5%). We checked the sensitivity of this calculation by looking at an increase, and separately a decrease, of 0.5 in the mean difference; and by varying the WP-ICC by ±0.05 and CAC by ±0.016 (which equates to ±20% of the base CAC). The trial has within the region of 80% power for all anticipated values of WP-ICC and CAC, and likely values of cluster-period sizes. The power curve, with the mean difference set as 6, is shown in figure 3B. As the CAC was particularly small, we separately explored the effects of a large CAC value (0.8) and found this had minimal impact.

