### Analysis plan

The primary outcome analyses will be performed according to the intention to treat. This will include all eligible patients for whom data have been obtained and will be analysed with respect to the treatment specified by the allocated randomisation order. The primary outcomes will be compared using two-sided tests and at a 2.5% significance level. Departures from randomisation at cluster level are defined as any cluster which does not switch to the intervention when stated in the randomisation order. A cluster is able to withdraw at any point during the trial. Per protocol analysis, which will exclude departures from randomisations and any cluster withdrawals, will also be completed for both primary outcomes of the trial. In situations where a pair of kidneys are transplanted as a ‘dual’ transplant into one recipient (eg, when the biopsy score is >4), this will be counted as half a transplant (in terms of utilisation, not as effective as performing two single transplants, but better than discard).

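### First primary outcome: the claim of about 80% power for all anticipated WP-ICC and CAC values is not supported when both adverse limits hold together (about 72% with 20 clusters, 76–77% with 22)

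*Protocol article*

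**What the plan says.** The section on the first primary outcome (Sample size calculations) gives a base case of WP-ICC 0.03, CAC 0.92, cluster-period size 18 and a rise from 28% to 39%, with a stated power of 85%. It then describes a sensitivity check: the baseline proportion is moved by 2 percentage points either way, the WP-ICC is varied ("lower WP-ICC set as 0 and upper WP-ICC set as 0.08"), and the CAC is varied from 0.74 to 1. The only result given for this check is one sentence: "The trial has within the region of 80% power for all anticipated values of WP-ICC and CAC, and likely values of cluster-period sizes". The text reports no power for any individual sensitivity case and does not say which cluster-period sizes count as likely.

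The legend to figure 3A gives the design behind the curves: "for 20 clusters, 5 steps, 4 clusters crossing over at each step and the proportion under control and intervention of 28% and 39" per cent. The curves themselves are not available in the text reviewed. The description of the study design says that 22 centres will be randomised, four or five at each step.

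**The concern.** The sentence covers all anticipated values of two parameters, and the anticipated ranges stand in the same paragraph. Read plainly, that includes a high WP-ICC together with a low CAC. Each makes the treatment effect harder to estimate. A low CAC does so because a larger share of the between-centre variation changes from period to period and does not cancel in the within-centre comparison, and this share matters more when the WP-ICC is high. The two adverse limits therefore compound.

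The article gives no other result for its robustness check. If the first primary outcome turns out null, readers will judge it against this sentence. At the joint corner the chance of missing the target effect would be about 28% with 20 clusters, or 23–24% with 22, against the 20% or so that the sentence suggests.

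**Working it through.** **Inputs, all from the protocol article**
- Test: "The primary outcomes will be compared using two-sided tests and at a 2.5% significance level" (Analysis plan), so z = 2.2414.
- Effect: "would represent an increase from 28% to 39% acceptance", so δ = 0.11.
- Size: "Assuming an average cluster-period size of 18" (4.38 offers per month × 4 = 17.5, rounded up).
- Design: 20 clusters, 5 steps of 4, hence 6 periods (figure 3 legend).
- Model: fixed period effect, random cluster effect, random cluster-by-period effect (sample size section and analysis plan).

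**Formulae**

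The outcome variance is the mean of p(1−p) over the two conditions: s² = (0.28×0.72 + 0.39×0.61)/2 = (0.2016 + 0.2379)/2 = 0.21975.

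For WP-ICC ρ, CAC c and size m:
- cluster variance: τ² = ρ c s²
- variance of a cluster-period mean about its cluster: σ² = ρ(1−c)s² + (1−ρ)s²/m

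The generalised least squares variance of the treatment effect, with I clusters and T periods, is

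Var = Iσ²(σ² + Tτ²) / [(IU − W)σ² + (U² + ITU − TW − IV)τ²]

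Here U is the number of intervention cluster-periods, W the sum over periods of the squared number of clusters exposed, and V the sum over clusters of the squared number of exposed periods.
- U = 4(5+4+3+2+1) = 60
- W = 4²+8²+12²+16²+20² = 880
- V = 4(25+16+9+4+1) = 220
- IU − W = 1200 − 880 = 320
- U² + ITU − TW − IV = 3600 + 7200 − 5280 − 4400 = 1120

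Power = Φ(δ/SE − 2.2414).

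**Base case (ρ = 0.03, c = 0.92, m = 18)**

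τ² = 0.006065 and σ² = 0.000527 + 0.011842 = 0.012369. Var = 20×0.012369×(0.012369 + 0.036391)/(320×0.012369 + 1120×0.006065) = 0.001122, so SE = 0.03350. δ/SE = 3.284 and power = 85.1%. The article's statement, "the trial will have 85% power (assuming a significance level of 2.5" per cent), is reproduced.

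**Both adverse limits (ρ = 0.08, c = 0.74, m = 18)**

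τ² = 0.013009 and σ² = 0.004571 + 0.011232 = 0.015802. Var = 20×0.015802×(0.015802 + 0.078055)/(320×0.015802 + 1120×0.013009) = 0.001511, so SE = 0.03888. δ/SE = 2.829 and power = 72.2%.

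**Grid at m = 18, 20 clusters**

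| WP-ICC | CAC | Power |
|---|---|---|
| 0 | any | 95.9% |
| 0.03 | 1 | 86.2% |
| 0.03 | 0.92 | 85.1% |
| 0.03 | 0.74 | 83.0% |
| 0.08 | 1 | 85.0% |
| 0.08 | 0.92 | 80.7% |
| 0.08 | 0.74 | **72.2%** |

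With the variance taken at the pooled proportion, the corner is 71.5%.

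**22 clusters**

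Three steps of 4 and two of 5 make 22. The same model gives about 88–89% in the base case. At the joint corner it gives 75.7% to 77.4%, depending on which steps take five centres (76.6% if the two larger groups are the first two or the last two).

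**eGFR, for comparison**

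With SD 16.06, difference 6, m = 8 and 20 clusters, the model gives 89.4% at WP-ICC 0.06 and CAC 0.08 (stated: 89%). Over WP-ICC 0.01 to 0.11 and CAC 0.064 to 0.096 the minimum is 80.3%. At the separately explored CAC of 0.8 with WP-ICC 0.11 it is 86.5%.

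**The case against.** The strongest reply is that the check was made one parameter at a time. The text does not say that both were set to adverse limits together, and the figure legend does not say whether its additional curves cross the two. On that reading every value at size 18 is 80.7% or more, and the sentence is right. This stands as far as it goes. However, the sentence is not limited in that way, and a reader cannot tell that the joint corner was left out.

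A second reply is that the wording promises only the region of 80%, and that 22 centres will be randomised. That also has force: 76–77% might arguably qualify. But the article's own calculation uses 20 clusters, and there the figure is 72%.

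Three stronger readings are tempting, and the article does not support them.
- **The sentence is simply false, or the trial is underpowered.** The base case reproduces, and the shortfall at size 18 needs both adverse limits at once.
- **Power is lower still because cluster-periods are smaller or centres vary in size.** Power would indeed fall, but the article names no range of likely sizes and gives no measure of variation, so any such figure rests on the reader's own assumption.
- **The same sentence fails for eGFR.** That sentence ("The trial has within the region of 80% power for all anticipated values of WP-ICC and CAC") does not cover the mean difference. Power falls below 80% at size 8 only if the difference is also cut to 5.5, which the article lists as a separate check.

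**Conclusion.** For the first primary outcome, the robustness statement is supported when WP-ICC or CAC is varied alone at size 18. It is not supported when WP-ICC is 0.08 and CAC is 0.74. Power there is about 72% on the 20 clusters of the calculation and about 76–77% on the 22 centres randomised. The shortfall is moderate: roughly 8 points and 3–4 points below 80%.

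These figures assume equal cluster-period sizes of 18, a normal approximation on the risk-difference scale, and the variance averaged over the two conditions. The same assumptions reproduce the stated 85%. The design, the target effect and the base-case power are not in question, and the eGFR statement needs no change on this account.

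**What to change.** In the section on the first primary outcome, replace the general sentence with the range found. Suggested wording: *At a cluster-period size of 18, power is 81% or more when WP-ICC or CAC is varied alone; when WP-ICC is 0.08 and CAC is 0.74 together, it is 72% with 20 clusters, or about 76–77% with 22.* State the number of clusters the figures rest on, and which cluster-period sizes were considered. If the sensitivity check was meant to vary one parameter at a time, say so.

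This changes text only. It needs no new data and no change to design or analysis. The cost is that one stated figure becomes less favourable.
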